### Ethical Considerations

The study will be carried out according to the Code of Ethics of the World Medical Association (Declaration of Helsinki). This protocol was reviewed and approved by the Ethical Board Committee of the Medical University of Silesia (decision no. KNW/0022/KB1/130/18/19). The trial is registered with reference number NCT03870828. All participants will sign the informed consent form prior to recruitment and will be informed of their right to waive consent at any time without a negative effect on their care. The informed consent form was reviewed and accepted by the Ethical Board Committee in terms of informativeness and understandability. The form allows for clinical data collection and secondary analysis. A copy of the form will be provided to each participant.

The study team will explain data analysis, the study duration, and objectives to the participants. We find it worth mentioning that in addition to drawing larger volumes of blood, storing biological fluids, and completing the questionnaires, no procedures beyond standard care will be performed. Therefore, participants will not be burdened with additional risks or prolongation of hospitalization/outpatient clinic visits. Study data will be deidentified to protect the privacy of participants. Data confidentiality will be maintained. No monetary compensation will be given to the participants. Voluntary participation and the time of the participants will be respected.

### Study Design

#### Phase 1

All patients meeting the inclusion criteria and not meeting the exclusion criteria regardless of prior treatment history will be recruited to phase 1 of the study. The recruitment process duration is estimated at 12 months. The previous recruitment of 40 patients led to a pilot study [7], which impacted further study design. The maximum number of patients included in this phase will be 80 (33.3%) in the IPAF group, 80 (33.3%) in the CTD-ILD group, and 80 (33.3%) in the IIP group.

#### Phase 2

Only patients with newly diagnosed disease (eg, no prior diagnosis of ILD and, hence, no prior treatment) will be recruited. The estimated recruitment duration is 36 months. The number of patients to be included in this phase will be 20 (33.3%) in the IPAF group, 20 (33.3%) in the CTD-ILD group (only those with RA, SSc, PM/DM), and 20 (33.3%) in the IIP group (only those with IPF, NSIP, COP, LIP; optimally 10, 50%, patients in the IPF subgroup and 10, 50%, in the non-IPF subgroup). Patients who were previously recruited to phase 1 of the study and meet the inclusion criteria of phase 2 may also be included.

Please see Figure 2 for a flowchart of the study design.

**Figure 2 figure2:**
[figure not shown]
Flowchart of the study design. CTD-ILD: connective tissue disease–associated interstitial lung disease; IIP: idiopathic interstitial pneumonia; IPAF: interstitial pneumonia with autoimmune features; V: visit.

#### Visit 1

A thorough medical history will be obtained using the Visit 1 questionnaire. During the first hospitalization, the following procedures will be performed:

Pulmonary function tests (PFTs)Depression and anxiety assessmentBlood analysisFiberoptic bronchoscopy (FOB) with bronchoalveolar lavage (BAL) and bronchial mucosa samplingThe 6MWTComputed tomography (CT)Transthoracic echocardiography (TTE)

#### Visit 2

Only patients who qualify for phase 2 of the study will have further visits (60 newly diagnosed patients). The following procedures will be performed after an average of 6 (SD 3) months from visit 1:

The Visit 2 questionnaireCough assessmentDyspnea assessmentDepression and anxiety assessmentPFTs, the 6MWT, and oxygen saturation (SpO2) measurementArterial blood gas (ABG) analysis (if indicated)

#### Visit 3

The following procedures will be performed after an average of 12 (SD 3) months from visit 1:

The Visit 2 questionnaireCough assessmentDyspnea assessmentDepression and anxiety assessmentPFTs and the 6MWTHigh-resolution computed tomography (HRCT)Blood sampling (including testing for autoantibodies and potential biomarkers)FOB with BAL (optionally, if clinically indicated)Capillary blood gas (CBG) analysisTTERheumatological consultation

#### Visit 4

The following procedures will be performed after an average of 24 (SD 3) months from visit 1:

The Visit 2 questionnaireCough assessmentDyspnea assessmentDepression and anxiety assessmentPFTs and the 6MWTHRCT (if clinically indicated)Blood sampling (including testing for autoantibodies and potential biomarkers)FOB with BAL (if clinically indicated)CBG analysis

#### Visit 5

The following procedures will be performed after an average of 60 (SD 3) months from visit 1:

The Visit 2 questionnaireCough assessmentDyspnea assessmentDepression and anxiety assessmentPFTs and the 6MWTHRCT (if clinically indicated)Blood sampling (including testing for autoantibodies and potential biomarkers)FOB with BAL (if clinically indicated)CBG analysisRheumatological consultation

### Diagnostic Procedures

#### Pulmonary Function Tests

PFTs will include spirometry with a reversibility test (in the case of obstruction), body plethysmography, and diffusion capacity for carbon monoxide (DLCO). Both absolute and predicted values will be recorded: forced expiratory volume in 1 second (FEV_1_), FVC, vital capacity (VC), FEV_1_/VC ratio, total lung capacity (TLC), diffusing capacity for carbon monoxide measured by the single-breath method (DLCO SB), inspiratory thoracic gas volume (ITGV), and residual volume/total lung capacity (RV/TLC) ratio. Cough assessment will be conducted using the Leicester Cough Questionnaire and numeric scale. Dyspnea assessment will be performed using the Likert scale and the Modified Borg Scale.

#### Depression and Anxiety

Depression and anxiety assessment will be conducted using the Hospital Anxiety and Depression Modified Scale (HADS-M) and the 9-item Patient Health Questionnaire (PHQ-9).

#### Blood Analysis

Briefly, a vein will be punctured in order to take a blood sample, and 30 mL of blood will be drawn. Next, 15 mL of plasma and 15 mL of full blood will be stored separately at –80°C. The following will be analyzed: N-terminal prohormone of brain natriuretic peptide (NT-proBNP) biomarkers routinely used during rheumatological workup and potential IPAF biomarkers. For this, 15 mL of venous blood will be drawn and divided into 2 parts (10 mL and 5 mL), and no anticoagulant will be added to the samples.

The first sample (10 mL) will be sent to the local laboratory for routine analysis of NT-proBNP and rheumatological factor (RF) and for anti–cyclic citrullinated peptide (anti-CCP) and antinuclear antibody (ANA) screening tests. In the case of the confirmed presence of ANAs and the determination of a fluorescence pattern (eg, homogenous, speckled, peripheral, nucleolar), further tests will be ordered: anti–double-stranded DNA (anti-dsDNA), anti-Smith (anti-SM), anti-SSA/Ro, anti-SSB/La, anti–topoisomerase I (anti-Scl70), and antiribonucleoprotein (anti-RNP) antibodies and myositis-specific autoantibodies, such as anti–histidyl-tRNA synthetase (anti-Jo1), anti–threonyl-tRNA synthetase (anti-PL7), anti–alanyl-tRNA synthetase (anti-PL12), anti–Mi2 antigen (anti-Mi2), anti–human exosome complex (anti-PmScl), and anti–melanoma differentiation–associated 5 (anti-MDA5) antibodies.

From the second sample of 5 mL, after clot formation, approximately 2.5 mL of serum will be separated and then divided into 5 portions of 0.5 mL each and placed in Eppendorf tubes. The samples will be marked according to a system allowing for patient anonymization: medical center symbol (sample number - type of biological material - date of sample collection, eg, A12-S_10/04/18). The samples will be stored at –70°C. They will be then used for IPAF biomarkers’ identification. This includes testing for chemokine C-C motif ligand 18 (CXCL18), surfactant protein (SP)-A, SP-D, Krebs von den Lungen-6 protein (KL-6), and chitinase 1 (CHIT1).

For genetic testing, 15 mL of full blood will be collected and divided into 10 Eppendorf tubes containing 1.5 mL of blood each. Samples will be marked according to the aforementioned organizational pattern and stored at –80°C.

#### Fiberoptic Bronchoscopy With Bronchoalveolar Lavage and Bronchial Mucosa Sampling

Before FOB, local anesthesia with lidocaine and conscious sedation with midazolam and optionally fentanyl will be performed according to detailed anesthesia protocols used in the endoscopy units of the respective medical centers taking part in the study. An intravenous cannula will be inserted prior to the procedure. During the endoscopy, the patient will be monitored according to safety protocols effective in the respective endoscopy units.

Bronchoalveolar lavage fluid (BALF) will be obtained from areas characterized by the greatest interstitial fibrosis involvement on HRCT. If such an area cannot be distinguished, BALF will be obtained from the middle lobe bronchus or the lingula on the side (B4, B5). Localization will be chosen based on HRCT results and will be recorded in the patients’ medical files. Next, 200 mL of sterile 0.9% saline solution, previously warmed to body temperature, will be inserted in parts through a 25 mL syringe to perform BAL. For the test to be deemed diagnostic, the protocol will target BALF salvage of at least 60%.

BAL will be performed according to the guidelines of the ERS [8] and the practical guidelines of the Polish Respiratory Society [9]. A differential cell count will be performed in every sample. BALF samples will be processed by an experienced laboratory technician based on Polish Respiratory Society guidelines [9].

Microscopic slide preparation, determination of cell viability, and determination of the dominant population will be performed according to standard laboratory procedures in the Polish Respiratory Society guidelines. The whole-cell count and cell viability will be measured in a sample derived from fluid that has undergone filtration or the first centrifugation. Samples will be prepared with the cytospin method (routinely 1200-2000 rpm for 10 minutes), and cellular smears will be assessed in cytospin samples stained according to the May-Grünwald-Giemsa method.

BALF samples will be secured for further tests, including testing for potential IPAF biomarkers. Briefly, 15 mL of BALF will be divided into 10 Eppendorf tubes containing 1.5 mL of BALF each and stored at –70°C. Low-speed centrifugal supernatants of BALF will be obtained from each sample. We will measure the concentration of potential biomarkers in each sample using the sandwich enzyme-linked immunosorbent assay (ELISA) technique.

Next, 5 mucosa samples will be obtained from the middle lobe bronchus for histopathological assessment later. Directly after sample collection, they will be put into dry Eppendorf tubes and frozen at –80°C. In addition, transbronchial lung cryobiopsy may be used to obtain material for histopathological assessment.

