According to Xue et al [22], a negative correlation of serum SP-A levels and the DLCO was revealed in the IIP group (which included 27/69 patients with IPAF, although this subgroup was not separately analyzed). A negative correlation was also revealed with FEV_1_ and the FVC [22]. This conclusion was partially confirmed by Wang et al [23], who revealed a negative correlation between serum SP-A levels and changes in the DLCO, FEV_1_, and FVC values after treatment. Additionally, Wang et al [23] suggested a prognostic role of SP-A: the pretreatment levels were found to be significantly lower than the posttreatment ones in individuals with progressive fibrosis during the course of IPAF. Moreover, a positive correlation was found between shifts in KL-6 and SP-A levels [23]. In a prospective study, Xue et al [24] observed a significant difference in serum SP-A levels measured at baseline and after 1-year follow-up. In individuals whose condition had exacerbated, SP-A levels were correlated with lung involvement scores on HRCT [24].

These findings need to be validated in European populations. There is a need to determine whether there is a correlation between lung involvement and a decrease in pulmonary function and SP-A/SP-D levels in the bodily fluids of patients with IPAF.

CHIT1 is a member of the glycosyl hydrolase family 18. It is expressed predominantly in polarized and differentiated macrophages and acts as an innate immune mediator digesting cell walls of pathogens that contain chitin (eg, fungi). CHIT1, due to its dysregulated activity, is a proposed marker in granulomatous and fibrotic ILDs associated with interstitial inflammation and lung tissue remodeling.

A study by Bargagli et al [25] revealed elevated CHIT1 activity in the BALF of individuals with IPF in comparison with the healthy control group; however, no significant differences in the serum levels were noted. This suggests the role of CHIT1 expression in interstitial macrophages in tissue injury and remodeling. We hypothesize that CHIT1 may play an important role in the pathogenesis of other ILDs, including IPAF, especially with a progressive fibrosing phenotype.

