Lee et al [26] revealed that in 2 different cohorts of individuals with SSc, CHIT1 activity and concentrations increased in the serum and BALF compared to demographically matched healthy controls. Individuals with SSc-ILD, in comparison with patients without lung involvement, were characterized by higher CHIT1 serum activity, which was also correlated with disease severity. The authors revealed that CHIT1 upregulates transforming growth factor beta 1 (TGF-β1) receptor expression and its signaling in fibroblasts, which makes CHIT1 a modulator of progressive interstitial lung fibrosis [27].

These findings raise the question whether CHIT1 or TGF-β1 and their interaction could be a potential target for SSc pharmacological therapy. As the etiopathogenesis of IPAF is still obscure, we plan to analyze both circulatory and lung activities of the enzyme to establish its potential role in the disease pathogenesis.

S100A9, also referred to as myeloid-related protein 14 or calgranulin B, is a member of the calcium-binding protein S100 family and is mostly expressed in neutrophils but also on vascular endothelial cells and mature macrophages. S1009A expression is enhanced by some chronic inflammatory factors [28]. It acts as an immunomodulatory, proinflammatory, and profibrotic agent [29]. It is mostly secreted in inflammatory lesions [30], and it has been suggested as a potential target for IPF treatment [31] and as a candidate biomarker to differentiate between IPF and other fibrotic ILDs [32]. However, convincing evidence from contemporary trials is yet scarce.

Elevated serum S100A9 levels have been reported in samples obtained from patients with RA, SLE, SSc, vasculitis, lung cancer, and various other diseases associated with chronic inflammation [33-35]. It has also been demonstrated that S1009A may promote atherosclerosis [36]. In an observational study by Lin et al [37], it was revealed that S100A9 levels were significantly elevated in BALF samples obtained from patients with severe IPF. It has also been demonstrated that S100A9 levels in the BALF of patients with IPF are positively correlated with the percentage of BALF neutrophils. This suggests a relationship between S1009A levels and disease activity. Some studies have reported that BALF S100A9 levels are significantly elevated in individuals with pulmonary involvement during the course of SSc [38,39].

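### As written, BALF is frozen before its supernatant is taken; this could bias BALF levels of markers made by lavage cells, clearly only CHIT1 on the measured panel

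*Protocol article*

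**What the plan says.** The section on fiberoptic bronchoscopy with bronchoalveolar lavage describes the biomarker samples in three consecutive steps.

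1. Aliquot and store: 15 mL of lavage fluid is "divided into 10 Eppendorf tubes containing 1.5 mL of BALF each and stored at" -70°C.
2. Spin: "Low-speed centrifugal supernatants of BALF will be obtained from each sample".
3. Assay: "We will measure the concentration of potential biomarkers in each sample using the sandwich enzyme-linked immunosorbent assay (ELISA) technique".

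The tubes in step 1 are said to hold BALF, not supernatant. No time point is attached to the spin in step 2.

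The same section mentions a separation step once before, for a different purpose: "The whole-cell count and cell viability will be measured in a sample derived from fluid that has undergone filtration or the first centrifugation". It also refers BALF processing in general to a national guideline, which is not shown.

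Under Blood Analysis, the serum for biomarker work is separated after clotting, then split into five 0.5 mL portions, then stored.

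On where the markers come from, the section on candidate biomarkers says of CHIT1: "It is expressed predominantly in polarized and differentiated macrophages". Of S100A9 it says that it "is mostly expressed in neutrophils but also on vascular endothelial cells and mature macrophages". It describes SP-A, SP-D and KL-6 as products of epithelial cells.

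**The concern.** Lavage fluid contains macrophages, neutrophils and other cells. If whole fluid is frozen, thawing can rupture them, and a later low-speed spin removes debris but not the protein already released. The measured level of a marker held inside those cells is then partly a measure of how many cells were in the tube.

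Two planned analyses would be exposed. The first is the comparison of BALF levels between IPAF, CTD-ILD and IIP: a group difference in cell yield could appear as a marker difference, or hide a real one. The second is the serum-versus-BALF comparison described in the Abstract, which is meant to separate systemic from local pathways. If serum is cell-free when frozen and BALF is not, that contrast also carries a difference in handling.

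The article also cites correlations of BALF CCL18 and S100A9 with BALF cell counts as evidence about disease. For a marker held in those cells, lysis would produce the same pattern.

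**Working it through.** **Volume.** 10 tubes × 1.5 mL = 15 mL, which agrees with the stated volume. The recovery target is at least 60% of 200 mL = 120 mL, so the banked part is 15/120 = 12.5% of it.

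**Order of steps, side by side.**

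| Material | Separation | Storage |
|---|---|---|
| Serum for biomarkers | stated, before aliquoting | after separation |
| BALF for cell count and viability | filtration or first centrifugation, stated | not applicable |
| BALF for biomarkers | low-speed spin, written after storage, no time point | before the spin, in written order |

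Where separation is meant to come first, the article says so for serum. It does not link the biomarker tubes to the filtration or centrifugation used for the cell count.

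**Which markers.** The panel named in the Abstract for serum and BALF is IL-8, TGF-β1, CXCL18, CXCL1, SP-A, SP-D, KL-6 and CHIT1.

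- CHIT1: macrophage source stated, so the concern applies.
- S100A9: neutrophil source stated, but it is not on this panel, so the concern applies only if it is measured.
- SP-A, SP-D, KL-6: epithelial source stated, so the concern is weaker.
- The others: the article does not describe them as held in lavage cells, so it does not settle the question.

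**Size, illustration 1 (assumed inputs).** Let E be the true extracellular level and L the contribution from lysed cells in a low-cell group, with s = L/(E + L). If another group has the same E but twice the cells, the apparent ratio is (E + 2L)/(E + L) = 1 + s. For s = 0 the ratio is 1.0, for s = 0.2 it is 1.2, and for s = 0.5 it is 1.5. The documents give neither s nor any cell counts.

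**Size, illustration 2 (assumed inputs).** Suppose there is no true marker difference. Let r be the correlation that lysis induces between level and cell count, and d the group difference in cell count in SD units. The spurious difference is δ = r × d in SD units. With n per group, the two-sided 0.05 pairwise rejection rate is Φ(δ/√(2/n) − 1.96) + Φ(−δ/√(2/n) − 1.96). Here n = 80 is the phase 1 maximum per group and n = 20 is the phase 2 group size.

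| r | d | δ | n = 80 | n = 20 |
|---|---|---|---|---|
| 0 | any | 0 | 0.050 | 0.050 |
| 0.1 | 0.3 | 0.03 | 0.054 | 0.051 |
| 0.3 | 0.5 | 0.15 | 0.158 | 0.076 |
| 0.5 | 0.8 | 0.40 | 0.716 | 0.244 |

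For example, with n = 80 and δ = 0.15: √(2/80) = 0.158 and 0.15/0.158 = 0.949, so the rate is Φ(−1.011) + Φ(−2.909) = 0.156 + 0.002 = 0.158.

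This normal two-group test stands in for the planned ANOVA or Kruskal-Wallis comparison. The effect is negligible if r or d is small and serious if both are moderate to large. Nothing in the documents says which case applies.

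**The case against.** The strongest reply is that sentence order is not chronology. The paragraph presents itself as a summary and never says that thawed tubes are spun or that cells remain in the frozen ones. Sentence order is loose elsewhere too: Blood Analysis mentions storage before it describes the draw and separation for biomarker work. Processing is referred to a guideline that may well require separation first, and tube-level handling is often left to a laboratory manual. This stands to the extent that freezing with cells is an inference and not a stated fact. It does not remove the point. The paragraph sets out its own steps, calls the stored material BALF and places the spin afterwards. With six centers, an order that can be read two ways can put two different materials under one label.

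A reader might infer that every BALF marker will track cell count. The documents do not support that: three panel markers are described as epithelial, and S100A9 is not on the panel.

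A reader might also take a 20% to 50% spurious difference as the expected size. That range comes only from assuming s between 0.2 and 0.5 and a doubling of cells. The documents bound neither, and do not report that cell yield differs between these groups.

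Nor is the problem wholly beyond repair. A differential count is planned for every sample and a whole-cell count is described, so levels can be checked against cells. That is only a partial remedy: the Statistical Analysis section specifies no such check, and adjusting for cell count could also remove genuine inflammatory signal.

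Finally, the stated primary purpose is the incidence of IPAF, which this does not touch.

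**Conclusion.** The point holds in a limited form. Followed in its written order, the section freezes unseparated BALF and takes supernatants afterwards; read leniently, it leaves the order open. Either way, a handling difference could enter the between-group and serum-versus-BALF comparisons. The documents support this clearly for CHIT1 only, and for S100A9 if it is measured.

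The direction and size cannot be estimated from the documents. The conclusion rests on two assumptions: that sites follow the sentence order, and that the guideline not shown does not already override it. Severity is should-fix for the laboratory arm, not must-fix for the study.

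**What to change.** Reorder the biomarker paragraph in the bronchoscopy section, for example: BALF will be filtered and centrifuged at low speed before aliquoting; the cell-free supernatant will be divided into ten 1.5 mL tubes and frozen; all centers will follow the same procedure.

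If any tubes have already been frozen unspun, flag them in the data set. Check their marker levels, CHIT1 first, against the planned cell counts in a sensitivity analysis, and report flagged and unflagged samples separately.

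The change is one sentence in the protocol and the matching laboratory instruction. It needs no extra sample or visit, and a centrifugation step is already mentioned for the cell-count sample. The downside is that biomarker fluid has to be processed on the day of bronchoscopy.
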